### Measures

As shown in Figure 1, assessment will be conducted at baseline and at 12-, 24-, and 36-month follow-ups. All assessments, each lasting approximately 60 minutes, will take place at the clinic during school breaks. Although all the adolescents living with HIV will be attending school and expect to be English-speaking (the instructional language in all Ugandan schools), assessments will be conducted in English or Luganda (the local language) depending on the English proficiency of the participants. All the interviewers will be fluent in English and Luganda. The questions will be translated from English to Luganda and back translated by a certified translator from a local university (Department of Languages) following standard procedures. The research team members who are fluent in Luganda and English will crosscheck all translated assessments. All the interviewers will receive highly structured and intensive training. Assessments will be conducted using standardized measures adapted from previous studies conducted in Uganda [104,133,141]. Any measures that have not been used will be pretested and made culturally appropriate to the Ugandan context. For questions measuring sensitive behaviors (eg, adherence), we will use audio computer-assisted self-interviews, where the participant takes the survey herself on a mini laptop. Nonsensitive questions will be administered by the interviewer. For the biological assay, blood specimens for HIV VL testing will be collected at baseline and 12, 24, and 36 months after the intervention. In accordance with the Abbott platform, VL will be dichotomized into undetectable (<40 copies/ml) and detectable (≥40 copies/ml) levels.

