To test these 3 hypotheses, we will fit a 3-level generalized linear mixed model (LMM) with fixed effects for the study arm, time, and their interaction. Our analysis will follow an intent-to-treat approach, such that all participants are included in the analyses, irrespective of whether they have complete or incomplete outcome data. Maximum likelihood (ML) and multiple imputation (MI) procedures will be used to address missing data with sensitivity analyses. Sensitivity analyses will be performed using pattern-based MI to examine the robustness of the results under different missing data assumptions. We will use random intercepts for school/clinic ID to account for clustering of persons within schools and their affiliated clinics and include random intercepts, random slopes, and their covariance for person ID to account for clustering of repeated measurements within persons. Reflecting the binary HIV viral suppression outcome, a binomial distribution and log link will be used to fit a log-binomial model to estimate the relative risks. If the log-binomial model does not converge, we will substitute a Poisson model with robust SEs [159,160]. To maximize rigor, quasi-likelihood methods will not be used. Instead, maximum likelihood estimation via adaptive Gaussian quadrature with 15 integration points will be used to ensure stable solutions [161]. To test hypotheses H1a to H1c, we will perform 3 time-averaged comparisons of repeatedly measured observations across study arms to examine the intervention effects over the duration of the study period. As all possible comparisons among the 3 study arms will be evaluated, the α will be set at .05/3=.017 for each of these 3 planned comparisons. Any additional post hoc comparisons (eg, paired comparisons of groups at each time point) will maintain a nominal α of .05 using simulation-based step-down multiple comparison methods [114]. Our team has considerable experience fitting 3-level generalized LMMs to analyze data from our cluster randomized asset-based intervention trials [113,162].

#### Primary Analyses for Aim 2

To examine the effect of M-Suubi on HIV stigma, we hypothesize the following:

H2a: MFG-HIVSR plus FEE will have lower mean HIV stigma than control participants (bolstered usual care).H2b: MFG-HIVSR plus FEE plus GED-HIVSR will have lower mean HIV stigma than control participants.H2c: MFG-HIVSR plus FEE plus GED-HIVSR will have lower mean HIV stigma than MFG-HIVSR plus FEE.

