To test these hypotheses, we will fit LMMs using the same fixed effects (study arm, time, and study arm-by-time) and random effects for the school/clinic (random intercepts) and person levels (random intercepts, random slopes, and their covariance) as proposed in the H1 analyses described earlier. To test hypotheses H2a to H2c, we will perform 3 time-averaged comparisons of repeatedly measured observations of stigma across study arms to examine the intervention effects over the duration of the study. To maintain a nominal type 1 error rate of 5% across tests of H2a to H2c, α will be set at .05/3=.017 for each planned time-averaged comparison. Our analyses will follow an intent-to-treat approach, and ML and MI approaches will be used to address missing data (as described in aim 1 earlier). To maximize rigor, the assumptions of normality and constant variance of residuals for these continuous outcomes in LMMs will be evaluated by examining histograms of the residuals and scatter plots of predicted values-by-Cholesky-scaled residuals, respectively. Transformations of outcomes will be used as needed to improve data conformance with model assumptions. Inferences for models whose residual statistics still do not fully meet assumptions following transformations will be generated via robust heteroskedastic-consistent Huber-White “sandwich” variance estimators [163]. All analyses will include outlier and influential case screening via the computation of Cook *D*, DF β values, and likelihood displacement statistics. If outliers are found, the results will be reported with and without outliers included [164,165].

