#### Randomization, Sample Size, and Power Analysis

We used NCSS Statistical Software Program PASS [166] to compute the minimum detectable effect size estimates for hypotheses H1a to H1c and H2a to H2c proposed to fulfill specific aims 1 and 2, respectively. For all power analyses, we assume power=0.80, α=.05/3=.017, and 4 repeated assessments from 714 participants conservatively assuming 15% attrition. Standardized minimum detectable effect sizes range from .26 to .35. Therefore, our study will have the power to detect small to medium effects for the proposed hypotheses

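### As written, the time-averaged H1 and H2 contrasts appear to include the pre-intervention baseline; if so, the post-baseline effect detectable with 80% power is about .35 to .47, not .26 to .35

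*Protocol article*

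**What the plan says.** Measures gives the schedule: "assessment will be conducted at baseline and at 12-, 24-, and 36-month follow-ups". Viral load follows the same visits: "blood specimens for HIV VL testing will be collected at baseline and 12, 24, and 36 months". There are therefore four assessments in all, and Results places intervention delivery after baseline and randomization.

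The Aim 1 model has "fixed effects for the study arm, time, and their interaction", with random effects for school/clinic and person. The section gives no baseline covariate and no constraint that the arms share a baseline mean. The test of H1a to H1c is stated as: "we will perform 3 time-averaged comparisons of repeatedly measured observations across study arms", with the aim of capturing intervention effects across the whole study period. Comparisons at single time points appear only as an example of post hoc work. Aim 2 uses the same fixed and random effects and tests H2a to H2c by "3 time-averaged comparisons of repeatedly measured observations of stigma across study arms".

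The section on randomization, sample size and power covers both sets of hypotheses. It takes power .80, a per-comparison alpha of .05/3 and "4 repeated assessments from 714 participants conservatively assuming 15% attrition", and reports: "Standardized minimum detectable effect sizes range from .26 to .35".

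No section lists the visits that enter the average. Nor does any say whether .26 to .35 is a difference averaged over four visits or an effect after baseline.

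**The concern.** The power section counts four repeated assessments for the hypotheses that the time-averaged contrasts test, and four is reached only by including baseline. The contrast wording covers the whole study period and excludes no visit. Read together, the two sections point to a four-visit average in which one visit has an expected arm difference of zero.

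Such an average answers a different question from the hypotheses, which concern effects of the intervention. It understates a post-baseline effect by a fixed fraction, and the quoted detectable effects then look smaller than the post-baseline effects the trial can detect. This touches all six planned comparisons for Aims 1 and 2, including those on the primary outcome. Baseline values are collected, but the stated model does not use them to sharpen the comparison.

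**Working it through.** **Inputs from the article.** 840 adolescents, 42 clinics, 14 per arm; 15% attrition; alpha .05/3; power .80; four assessments; detectable effects .26 to .35. Sidedness is not stated, and two-sided is assumed.

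**1. Analysed sample.** 840 × 0.85 = 714, which is 714/3 = 238 per arm and 714/42 = 17 per clinic. This agrees with the article.

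**2. The stated detectable effects.** They cannot be reproduced from the article alone, because it gives neither the clinic intraclass correlation (ICC) nor the within-person correlation (r). For a standardized continuous outcome with compound symmetry and T visits:

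V = ICC + (r − ICC)/17 + (1 − r)/(17T), detectable difference = (2.394 + 0.842) × √(2V/14), multiplier 3.236.

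Assume r = .5 and T = 4:
- ICC .01: V = .01 + .0288 + .0074 = .0462, detectable difference .263.
- ICC .05: V = .05 + .0265 + .0074 = .0838, detectable difference .354.

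These match .26 to .35 after rounding. The match makes the assumptions plausible but does not identify them, because other pairs give values in the same range.

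**3. Dilution if baseline is averaged in.** With equal weights the tested quantity is (0 + d12 + d24 + d36)/4. If the three later differences all equal d, this is 0.75d.

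**4. Post-baseline effect needed for 80% power.** .26/0.75 = .347 and .35/0.75 = .467, so about .35 to .47.

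**5. The same result as power.** If d equals the stated detectable effect, the standard error cancels and no correlation is needed:

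Φ(0.75 × 3.236 − 2.394) = Φ(0.033) = .513.

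Variants: 51.4% with alpha rounded to .017; 54.0% one-sided; 51.3% to 51.4% with t references on 26, 39 or 708 degrees of freedom.

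**6. If the effect is not constant.** The intervention runs for 20 months, and Results counts follow-up from baseline, so the month-12 effect may be partial. If it were half (an assumption), the factor is (0 + 0.5 + 1 + 1)/4 = 0.625 and power is about 36%.

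**7. If baseline is left out of the contrast.** Under the assumptions of step 2 with T = 3, the detectable difference is .270 (ICC .01) to .359 (ICC .05). Across r from .3 to .7 and ICC .01 to .05, power at the four-visit detectable effect is about 76% to 79%.

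**The case against.** The strongest reply is that the article never lists the visits in the average. It speaks of intervention effects, which cannot exist before the intervention, and an arm-by-time model can yield a contrast over months 12, 24 and 36 without any change. The four assessments in the power section may describe the data entering the model. This stands to the extent that baseline inclusion is a strong inference and not an explicit statement. It does not clear the article, however: on that reading, the number of visits behind the tested difference is three, and the power section says four.

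A reader might also infer that the trial simply has 51% power instead of 80%. The article does not support that. There, .80 is an input and the detectable effect is the output. If .26 to .35 is the four-visit averaged difference, power at that value is 80% by construction. The 51% needs .26 to .35 to be read as a constant post-baseline effect.

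Two further readings go too far. Chance baseline imbalance between 14 clinics per arm is not a bias in a randomized comparison. It is variance, already carried in the standard error. Nor can a definite gain from baseline adjustment be promised. With r = .5, ICC .01 to .05 and clinic effects perfectly stable over three years, the detectable effect would be about .20 to .22. With r = .3 it is .21 to .24. At r = .5 and ICC .05, a clinic-effect correlation over time of .8 gives about .24, and one of .5 gives about .26. The article states none of these correlations.

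**Conclusion.** The point holds in conditional form. As written, the contrast appears to include baseline. If it does, and visits are weighted equally, a constant post-baseline effect is cut to three quarters and the post-baseline effect detectable with 80% power is about .35 to .47. If it does not, the visit count in the power section is wrong, but the consequence is small: about .27 to .36 against .26 to .35 under the assumed correlations. Either the contrast or the count has to change.

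The factor of three quarters needs no correlation; it rests on equal visit weights and a constant effect after baseline. The power figures use a standardized continuous scale, so for the binary viral suppression outcome with a log link they are approximate. An unconditional statement that the primary estimate is biased by a quarter, or that power is 51%, would go beyond what the article says.

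**What to change.** - In the Aim 1 and Aim 2 analysis sections, define the H1 and H2 contrasts as the arm difference averaged over months 12, 24 and 36, with the visit weights stated.
- Adjust for the baseline value of the outcome (viral suppression for H1, stigma for H2), or keep baseline in the longitudinal model with the arms constrained to a common baseline mean. This is recommended for precision; the size of the gain depends on correlations that should be stated.
- In the power section, restate the detectable effects on three post-baseline assessments, give the ICC and within-person correlation used, and say that the effect size refers to the post-baseline average.

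The cost is the wording of two contrasts and one recomputed power paragraph. Baseline is already collected, so no visit, sample or participant is added.

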## Methods

### Study Overview

M-Suubi is a 5-year multilevel mixed methods randomized controlled trial. As shown in Figure 1, the M-Suubi intervention will be evaluated using a 3-arm cluster randomized trial implemented across 42 community health centers (with HIV clinics), targeting adolescents living with HIV aged 10 to 17 years and attending primary and secondary schools with a boarding section (n=14 clinics per arm; n=280 students per study arm). Adolescents living with HIV will be randomized at the clinic level to one of the three study conditions: (1) bolstered usual care, (2) MFG-HIVSR plus FEE, and (3) MFG-HIVSR plus FEE plus GED-HIVSR (Figure 1). M-Suubi will be provided for 20 months, with assessments at baseline and 12, 24, and 36 months.

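### Bonferroni at .05/3 for the three pairwise contrasts in H1 and in H2 is valid, but Shaffer's step-down test keeps every rejection it makes, adds others, and still holds familywise error at 5%

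*Protocol article*

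**What the plan says.** Under Primary Analyses for Aim 1, the Protocol article tests three time-averaged contrasts of viral suppression: family arm against control (H1a), combined arm against control (H1b), and combined arm against family arm (H1c). It divides alpha by three: "the α will be set at .05/3=.017 for each of these 3 planned comparisons". The reason given is the number of contrasts: "As all possible comparisons among the 3 study arms will be evaluated". Further post hoc comparisons, such as pairs of arms at single time points, "will maintain a nominal α of .05 using simulation-based step-down multiple comparison methods".

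Primary Analyses for Aim 2 applies the same division to stigma ("α will be set at .05/3=.017 for each planned time-averaged comparison") and states the purpose as follows: "To maintain a nominal type 1 error rate of 5% across tests of H2a to H2c". The power section uses that alpha too: "we assume power=0.80, α=.05/3=.017, and 4 repeated assessments from 714 participants conservatively assuming 15% attrition". It reports standardized minimum detectable effects of .26 to .35.

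The hypotheses are worded directionally. The article does not say whether the tests are one- or two-sided, and it gives no sequential or closed rule for the planned contrasts.

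**The concern.** Bonferroni guards against every pattern of true and false nulls among three hypotheses. Three arms do not allow every pattern. If two of the pairwise equality nulls hold, the third holds as well, so exactly two true nulls cannot occur. A rule that stays at .05/3 for all three contrasts, whatever the others show, protects against a situation that cannot arise.

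The power given up falls on the second and third rejections. H1c matters most here. The section on Treatment Arm 2 says that the educator component was added to test its extra benefit, and H1c is the contrast that answers that question. Once both active arms clearly beat control, H1c is the only null that can still be true, yet it is tested at about a third of the error rate that the plan allows. The number of clinics is fixed, so a better testing rule adds power without further recruitment.

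**Working it through.** **Inputs from the article.** Alpha .05/3 for each contrast; power 0.80; three arms of equal size ("n=14 clinics per arm; n=280 students per study arm"); 714 participants after 15% attrition. **Assumptions.** Two-sided tests (sidedness is not stated) and arm estimates that are approximately normal with equal variance.

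**The plan's own figures.**
- .05/3 = .01667, printed as .017. Used literally, 3 × .017 = .051, a trivial rounding effect.
- 840 × 0.85 = 714, or 714/3 = 238 per arm.
- The detectable-effect range cannot be reproduced exactly, because the article gives neither the clinic intraclass correlation nor the within-person correlation. With one measurement and no clustering, (2.394 + 0.842) × √(2/238) = 3.236 × 0.0917 = .297. Assumed within-person correlations of .3 to .9 and clinic intraclass correlations of 0 to .05 give about .20 to .39, which contains the stated .26 to .35.

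**Why Shaffer's test controls the error.** Its rule is to reject the smallest p-value if it is at or below .05/3, and then to test the other two contrasts at .05 each. Under two-sided equality nulls there are three cases.
1. All three nulls true. A false rejection needs the smallest p-value to be at or below .05/3, which has probability at most 3 × .05/3 = .05.
2. Exactly one null true. Only that one can be falsely rejected, and this needs its p-value to be at or below .05.
3. Exactly two nulls true. Impossible with three arms.

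Familywise error is therefore at most 5%. Any contrast with p at or below .05/3 is still rejected, because the first step is then passed and the contrast also meets .05.

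**Size of the gain.** The three arm estimates were simulated (1,000,000 draws). The effect d is the difference at which one contrast has 80% power at .05/3: d = 2.394 + 0.842 = 3.236 standard errors of a contrast. Arms are listed in the order control, family, combined.

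| Scenario | Quantity | Bonferroni | Shaffer |
|---|---|---|---|
| All arms equal | familywise error | .044 | .044 |
| One pair equal, third arm far away | familywise error | .017 | .050 |
| 0, d, d | power, H1a and H1b each | 80% | 86% |
| 0, d, d | power, H1a and H1b both | 69% | 81% |
| 0, d, d | at least one rejection | 91% | 91% |
| 0, d/2, d | power, H1b | 80% | 81% |
| 0, d/2, d | power, H1a and H1c each | 22% | 35% |
| 0, d, 1.5d | power, H1c | 22% | 37% |
| 0, d, 2d | all three rejected | 61% | 80% |

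Shaffer's test lost no Bonferroni rejection in any scenario.

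**Closed tests.** A closed test that starts from a Tukey-range global test also lost none. One that starts from a 2-df Wald test did lose some. A single contrast passes Bonferroni at z² = 2.394² = 5.73, but the Wald gate needs 5.99. Up to about 0.4% of simulated trials lost a Bonferroni rejection this way, the most in the 0, d/2, d scenario.

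**The case against.** The strongest reply is that nothing here is an error. Bonferroni is valid, it is applied in the same way to H1 and H2, it meets the stated 5% aim, and the trial was powered at that alpha. All of this stands, and the point is one of efficiency only.

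Several stronger readings are tempting, and the documents do not support them.
- *That the power is given up for nothing.* Single-step Bonferroni yields simple simultaneous intervals, which has some value in a trial that reports relative risks. The article does not ask for such intervals, but the trade-off is real.
- *That the trial becomes more likely to show some effect.* Under Shaffer's test the chance of at least one rejection is unchanged. Only the later rejections gain.
- *That the detectable effect falls by 13%.* The ratio (1.960 + 0.842)/3.236 = .866 applies only to a contrast tested at .05 after the first step has been passed. It is not a reduction in the trial's detectable effect.
- *That H1c is rescued.* The 22% to 35% gain rests on an assumed half-size educator effect that the article does not give, and 35% is still far below 80%.
- *That the plan contradicts itself by using "simulation-based step-down multiple comparison methods" for post hoc comparisons.* A larger and more open-ended family can reasonably be handled differently from three fixed contrasts. The sentence shows only that step-down testing is already acceptable to the team.

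The directional wording of the hypotheses is a fair difficulty. For one-sided nulls the logic in the working fails. For example, the combined arm could be better than the family arm while neither is better than control, which leaves two nulls true and the third false. The two-sided choice therefore has to be written down. Holm's procedure needs no such logic, loses no Bonferroni rejection, and still raises H1c from 22% to 28% (0, d/2, d) or from 22% to 35% (0, d, 1.5d).

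**Conclusion.** The point holds as an inefficiency that is worth correcting. For three pairwise contrasts with two-sided equality nulls, Shaffer's test rejects everything that Bonferroni rejects, and sometimes more, with familywise error at or below 5%. At the planning effect, a contrast with 80% power moves to between 81% and 90%, depending on where the third arm lies. Smaller contrasts gain about 13 to 15 percentage points.

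The error control rests on two-sided equality nulls, and the power figures also on approximately normal arm estimates of equal variance. The power scenarios are illustrations, not predictions from the article. The detectable effects in the power section need no revision, because they remain correct as conservative figures.

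**What to change.** In Primary Analyses for Aim 1, and likewise for Aim 2, replace the fixed .05/3 rule with two sentences: all tests are two-sided; the contrast with the smallest p-value is rejected if that p-value is at or below .05/3, and if so the other two are each tested at .05. Apply this separately to H1 and to H2, and settle it before any unblinded analysis.

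A closed test is an acceptable alternative only if its global test is named as min-p or Tukey-range, not a 2-df Wald test. If two-sided testing is not wanted, Holm's procedure is the safe choice.

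The cost is in reporting. Simultaneous intervals that match a step-down test are less simple. Bonferroni intervals can still be shown, with a note that such an interval may include no effect for a contrast that Shaffer's test rejects.
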